**PART II – BEGIN INTERVIEW**

READ: Hello. My name is < > and I am working with < > on a study coordinated by < > that will improve HIV prevention programs. I would like to ask you some questions about this site. I can offer you this information sheet that has more information about the study. This should take about 30-40 minutes.

| NO.        | QUESTION                                                                                                                                                                                                                                                                                                                        |                                                                    | RESPONSE                                                                                     |  |
|------------|---------------------------------------------------------------------------------------------------------------------------------------------------------------------------------------------------------------------------------------------------------------------------------------------------------------------------------|--------------------------------------------------------------------|----------------------------------------------------------------------------------------------|--|
| Q10
A-C | INSTRUCTIONS TO THE INTERVIEWER (DO NOT READ ALOUD):
A. DID YOU READ THE INFORMATION SHEET TO THE RESPONDENT?
B. DID YOU READ THE CONSENT FORM TO RESPONDENT IN LANGUAGE RESPONDENT UNDERSTANDS?
C. HAVE YOU ASKED THE RESPONDENT IF HE/SHE HAS QUESTIONS, AND HAVE YOU ANSWERED THOSE QUESTIONS? |                                                                    | 
Yes No
 A. 1 2
B. 1 2
C. 1 2 |  |
| Q11        | Are you willing to answer the questions I will ask you?                                                                                                                                                                                                                                                                         |                                                                    | 
Yes No
 1 2                                             |  |
| Q12        | What is your age?                                                                                                                                                                                                                                                                                                               | IF RESPONDENT IS YOUNGER THAN 18, STOP INTERVIEW AND FIND ANOTHER. | WRITE AGE IN YEARS:                                  |  |
| Q13        | Do you work here?                                                                                                                                                                                                                                                                                                               |                                                                    | 
Yes No
 1 2                                             |  |

|     |                                                               |                    |
|-----|---------------------------------------------------------------|--------------------|
| Q14 | Were you born as a male or female?                            | MALE 1
FEMALE 2 |
| Q15 | Do you currently identify more as a male or more as a female? | MALE 1
FEMALE 2 |

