### B. Study Populations

The study populations are sex workers, MSM and transgender women, at least 15 years of age who are residents of a to-be-defined geographic area at time of interview. International definitions of key populations follow:

- Sex worker (from the UNAIDS Guidance Note on HIV and Sex Work): “female, male and transgender adults and young people who receive money or goods in exchange for sexual services, either regularly or occasionally”. This definition includes those who occasionally exchange sex for gifts. It does not include people younger than 18.
- Men who have sex with men: MSM is an abbreviation used for ‘men who have sex with men’ or ‘males who have sex with males’. The term ‘men who have sex with men’ describes males who have sex with

males, regardless of whether or not they have sex with women or have a personal or social gay or bisexual identity. This concept is useful because it also includes men who self-identify as heterosexual but have sex with other men. However, abbreviations should be avoided whenever possible. Writing out the term is preferred.

- Transgender persons: ‘individuals whose gender identity and/or expression of their gender differs from social norms related to their gender of birth. The term transgender persons describes a wide range of identities, roles and experiences which can vary considerably from one culture to another.’

Operational population definitions and inclusion criteria will be established either through the mapping readiness assessment or during data analysis based on participants’ responses to the behavioral questionnaire.

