#### ***Step 4: Key population interviews among site workers and patrons; HIV, CD4 and STI testing Selection of Sites and Events for Worker and Patron Surveys and Testing***

Individual interviews and HIV testing with male and sex workers, men who have sex with men and transgender women will be performed in a sample of sites and events visited in the previous step. Social mobilizers will assist interviewers in identifying sex workers, men who have sex with men and transgender women at venues. At venues where social mobilizers accompany interview teams, all people identified by social mobilizers as potentially people from key populations will be interviewed. Additionally, people at venues will be approached randomly by interviewers and will not be screened for eligibility based on history of sex worker or same-sex practices. Through random selection, some participants may not be sex workers, MSM or transgender people.

Sites will be selected using a systematic fixed-interval sampling strategy with the probability of selection proportional to the size of the site. The size of a site is defined by the number of people socializing at the venue during a busy time as reported by the site informant. A sampling frame of sites that were confirmed to exist and be in operation and those that were temporarily closed during site visits (Step 3) will be constructed, with sites and events sorted by province/geographic area, type and size. Prior to interval selection, venues eligible for individual interviews are sorted by geographic location, as indicated by geographic code, and size of venue.

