#### *Inclusion Criteria for PLACE*

Male and female participants who meet the following eligibility criteria will be invited to participate in the project:

- At least 15 years of age at time of interview and not accompanying or running an errand for parents
- Recruited at selected venues
- Consent to participant in a face-to-face structured behavioral survey and provide written informed consent with initials or an X

Additionally participants that meet one of the following inclusion criteria for key populations will be offered additional STI testing:

- At least one sexual contact for cash in the last 12 months
- Man or transgender woman that has had oral or anal sex with another man in the past 12 months
- Identification as a male-to-female transgender woman

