#### *Consent Process for Individual Interviews with Venue Patrons and Workers*

Interviewers will explain to site patrons and workers the purpose of the study, type of questions asked, and that minimal information will be collected from them. The interviewer will review an informed consent statement that describes risks and benefits of participating in the interview, HIV and STI testing, along with the procedure. Subjects will initial or write an "X" on the consent form acknowledging their consent to participate. They will then be provided a copy of the consent form to keep (Appendix 9).

Site patrons and workers, MSM and transgender women will be required to provide written consent by initialing or marking an "X" on the consent document. This mode of consent avoids excluding the significant portion of the potential subject pool that is not be able to sign their name and diminishes the social, psychological, and economic risks to participants should a breach of confidentiality occur, as initials would be more difficult to definitively link to a given subject. We do not collect subject names on the survey questionnaire itself, in order to protect participant confidentiality/privacy given the sensitive nature of some of the questions regarding individual sexual and drug use behavior.

Subjects aged 15-17 who wish to participate in the study will be allowed them to provide independent consent which would be documented with their initialing or marking an X on a written consent form. Subjects age 15-17 will be asked if at the time of the interview, they are accompanied by their parents or if they are running an errand for their parents. Only minors who are not accompanied or running an errand will be asked to participate. Participation in the study may facilitate access to the crucial service of HIV testing for adolescents who may face greater stigma or embarrassment requesting testing at other clinics. Adolescents aged 15-17 have been included in many previous PLACE studies, as they are often among those at highest risk for HIV and other sexually transmitted infections. Furthermore, most of the adolescents eligible for this study will have been identified by nature of visiting a venue where people go to meet sexual partners.

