### **E. Sample Size**

The sample size will be calculated based on the budget and the estimated number of sex workers, men who have sex with men and transgender women that are thought to be reachable (Table 3). For PLACE/Programmatic mapping the exact number of each population interviewed will depend on the site identification, verification and patron and worker interview steps.

Approximately 2000 men and women will be interviewed and tested for HIV at venues in Luanda. We expect to recruit approximately 600 sex workers, 600 men who have sex with men and 200 transgender women. Around 600 participants could be from the general population. Approximately 400 female sex workers will be recruited in Cabinda using RDS.

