| 
B7
            | 
On a busy day, how many women aged 18 and older come here as patrons (to socialize, drink alcohol, etc.) over the course of the entire day and night?
 
READ OPTIONS. CIRCLE ONE CODE BETWEEN 0 AND 13 THAT INDICATES THE CORRECT RANGE.
                                                                                                                                                                                 | 
CIRCLE ONE CODE BETWEEN 1 AND 13:
 
 
 0	1	
 
 1-14	2	
 
 15-29	3	
 
 30-49	4	
 
 50-99	5	
 
 100-149	6	
 
 150-199	7	
 
 200-299	8	
 
 300-399	9	
 
 400-499	10	
 
 500-999	11	
 
 1000-1999	12	
 
 Over 2000	13	
 
 |                                                               | 0 | 1 | 1-14 | 2 | 15-29 | 3 | 30-49 | 4 | 50-99 | 5 | 100-149 | 6 | 150-199 | 7 | 200-299 | 8 | 300-399 | 9 | 400-499 | 10 | 500-999 | 11 | 1000-1999 | 12 | Over 2000 | 13 |

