**SECTION C -CONTINUE INTERVIEW IF RESPONDENT IS A MEMBER OF A KEY POPULATION**

| NO. | QUESTION                                                                                                                                                                                                                                                                                                                       | RESPONSE                                                                                                                                            |
|-----|--------------------------------------------------------------------------------------------------------------------------------------------------------------------------------------------------------------------------------------------------------------------------------------------------------------------------------|-----------------------------------------------------------------------------------------------------------------------------------------------------|
| C1  | 
In the past 7 days, on which days did you come here?
 
START WITH TODAY AND THEN GO BACK DAY BY DAY FOR THE PREVIOUS 6 DAYS.
FOR EXAMPLE IF TODAY IS WEDNESDAY, CIRCLE YES FOR WEDNESDAY AND THEN ASK ABOUT TUESDAY, THEN MONDAY, ETC.
 
WHEN YOU ARE FINISHED, EVERY DAY SHOULD HAVE A YES OR NO ANSWER.
 | 
Yes No
 
Saturday 1 2
 
Friday 1 2
 
Thursday 1 2
 
Wednesday 1 2
 
Tuesday 1 2
 
Monday 1 2
 
Sunday 1 2
 |
| C2  | In the past 4 weeks, how many times did you come here including today?                                                                                                                                                                                                                                                         | NUMBER:_____                                                                                                                                        |
| C3  | In the past 12 months, have you met a new sexual partner here?                                                                                                                                                                                                                                                                 | 
Yes No
 
1 2
                                                                                                                            |

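### Form C stops the interview at under 18 and at non-key-population status, although the protocol enrols from age 15 and needs the answers of every venue participant

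*Protocol*

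**What the plan says.** **Age.** Section VI.B states: "The study populations are sex workers, MSM and transgender women, at least 15 years of age". The PLACE inclusion criteria in VI.C, Step 4 repeat the limit: "At least 15 years of age at time of interview and not accompanying or running an errand for parents". The consent section for venue patrons and workers adds: "Subjects aged 15-17 who wish to participate in the study will be allowed them to provide independent consent". Against this, Form C Q12 instructs: "IF RESPONDENT IS YOUNGER THAN 18, STOP INTERVIEW AND FIND ANOTHER". Section VI.B is also not uniform: the sex-worker definition it cites excludes people under 18.

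**Who answers Section C.** The heading of Section C in Form C reads: "CONTINUE INTERVIEW IF RESPONDENT IS A MEMBER OF A KEY POPULATION". Step 4 says that people approached at random "will not be screened for eligibility based on history of sex worker or same-sex practices", and it expects some of them not to be key population. The Sample Size section plans about 2,000 interviews with HIV tests at Luanda venues and says: "Around 600 participants could be from the general population".

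**Site counts.** Form B item B7 asks "how many women aged 18 and older come here as patrons". These site-informant counts feed the population size estimates in section VIII.C, which then serve as coverage denominators.

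**The concern.** A skip rule decides what is collected. If field staff or the smartphone programme follow Form C as printed, an age group that the protocol enrols, and describes as often at highest risk, drops out of the venue survey. Adults outside the key populations give no behavioural or service data, so the objective in section V of characterising men and women at venues and finding gaps in their HIV prevention services cannot be met for them.

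The Section C limit is also circular. For sex workers and MSM, Form C has nothing before Section C that could tell the interviewer whether to continue. A member of either group who is not recognised by sight or by a social mobilizer is treated as general population.

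**Working it through.** **1. The plan's Luanda figure.** Components from the Sample Size section: 600 sex workers, 600 MSM, 200 transgender women, around 600 general population.

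600 + 600 + 200 + 600 = 2,000, which reproduces the stated total.

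**2. Reach of the Section C limit.** If the general-population figure is 600, 600 / 2,000 = 30% would have no Section C data, leaving at most 2,000 − 600 = 1,400 with it.

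**3. What each group keeps under the printed rules.**
- *Ages 15-17:* stopped at Q12, so only the age is recorded. Step 4 brings respondents to HIV testing after the interview, so a stopped minor is replaced by someone else and not tested.
- *Adults not key population:* Q12-Q15 (age, works at site, birth sex, current gender) and the HIV rapid test, which Table 1 lists for the general population.
- *Adults recognised as key population:* the full form.
- *Sex workers and MSM not recognised:* as for the general population, and no questionnaire-based STI test offer.

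**4. Can the limit be applied?** Q14 and Q15 can flag a transgender respondent. Anal sex with a man (C10) and money for sex (C11, C12) are asked only inside Section C. Form B shows the contrast: there B25 asks about selling sex and sex between men before the form decides whether to continue.

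**5. Where the protocol needs the answers from everyone.**
- Section V: characterise venue visitors and identify gaps in HIV testing, condoms and STI management. All these individual-level items sit in Section C.
- Step 4, description of Form C: it is to obtain sexual history and prior exposure to testing and prevention from the individual interviewed.
- Risk assessment and collection of biologic specimens: the offer of further STI tests is decided from the behavioural questionnaire.
- Section VIII.B: venue attendance is one of the inputs named for the weights. It is recorded at C1, C2 and C4, also behind the limit.

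**6. Number aged 15-17.** The protocol gives no share. Purely as an assumption, 2%, 5% or 10% of the 1,400 would be 28, 70 or 140 people. Because the rule says to find another respondent, they might be replaced by adults, so the loss is one of age coverage and not necessarily of sample size.

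**7. Age base of Form B.**
- Limited to 18 and older: B7 and the items that follow from it (B8-B10); B13 and B14.
- No age limit: B5-B6 (women working at the site), B11 (men present), B15 (transgender people).
- B13 and B14 refer to the B12 count as men aged 18 or older, although B11, which B12 refines, has no age limit.

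The counts therefore do not share an age base with one another or with a survey from age 15.

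**The case against.** The appended forms are visibly unadapted templates. The electronic version is still to be built and pre-tested, and Step 1 provides for a pilot and revision. That stands to this extent: the loss is conditional on the forms being used as printed. It does not remove the contradiction, since nothing in the protocol marks these two rules for change, and a pre-test aimed at unclear questions may pass a clear but wrong skip.

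Step 4's statement about not screening concerns who is approached and enrolled; a later skip makes nobody ineligible. That is fair. The case against the Section C limit rests mainly on section V, the description of Form C and the STI test rule.

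Several stronger readings are tempting but unsupported:
- *That the general venue population would have no data.* They keep Q12-Q15 and an HIV result.
- *That 600 general-population interviews are fixed.* The text says only that there could be around 600, and Table 3 sets no number for other men and women at venues.
- *That the parents-or-errand check is missing because Form C lacks it.* The consent section says minors will be asked, and it may be handled there.
- *That all Form B key-population counts are for adults.* Only some are.
- *That prevalence is biased towards visible members because of Form C.* Recruitment already relies on social mobilizers identifying people, so the effect cannot be attributed to the form alone.
- *That the rules were carried over from Form B.* The matching wording makes this plausible, but the protocol does not say so.

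**Conclusion.** The point holds as an internal contradiction that must be resolved before fieldwork. Followed as printed, Form C gives no interview data beyond age for 15-17-year-olds and no Section C data for adults outside the key populations. The latter could be around 600 of about 2,000 in Luanda (30%), if the protocol's tentative figure is met. Sex workers and MSM not identified in advance lose the same data and the STI test offer; their number cannot be estimated from the protocol.

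The size of the under-18 loss is unknown, and the conclusion does not depend on it. A reader might infer that the protocol body is settled at 15 and only Form C is wrong. It is not: section VI.B carries both 15 and, in the cited sex-worker definition, 18. The passages must be reconciled, and this review does not say which age is right.

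**What to change.** - **Section C limit.** Delete it, so that every consenting participant answers Section C. Derive key-population status from C10-C12 and Q14/Q15, using C11 for the 12-month sex-work criterion. C10 asks only about anal sex while the inclusion criterion counts oral or anal sex, so align the two.
- **Age.** State one lower limit and carry it through section VI.B, the PLACE inclusion criteria, the consent section and Form C Q12. If ages 15-17 remain eligible, say where the accompanied-or-errand check is recorded.
- **Form B.** Put B5-B15 on one age base that matches the survey, or state the age range to which the size and coverage estimates apply.

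The cost is reprogramming two skips, editing a few item stems and correcting the protocol text before fieldwork, plus a longer interview for general-population respondents.

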**SECTION C -CONTINUE INTERVIEW IF RESPONDENT IS A MEMBER OF A KEY POPULATION**

| NO. | QUESTION                                                                                                                                                                                                                                                                                                                       | RESPONSE                                                                                                                                            |
|-----|--------------------------------------------------------------------------------------------------------------------------------------------------------------------------------------------------------------------------------------------------------------------------------------------------------------------------------|-----------------------------------------------------------------------------------------------------------------------------------------------------|
| C1  | 
In the past 7 days, on which days did you come here?
 
START WITH TODAY AND THEN GO BACK DAY BY DAY FOR THE PREVIOUS 6 DAYS.
FOR EXAMPLE IF TODAY IS WEDNESDAY, CIRCLE YES FOR WEDNESDAY AND THEN ASK ABOUT TUESDAY, THEN MONDAY, ETC.
 
WHEN YOU ARE FINISHED, EVERY DAY SHOULD HAVE A YES OR NO ANSWER.
 | 
Yes No
 
Saturday 1 2
 
Friday 1 2
 
Thursday 1 2
 
Wednesday 1 2
 
Tuesday 1 2
 
Monday 1 2
 
Sunday 1 2
 |
| C2  | In the past 4 weeks, how many times did you come here including today?                                                                                                                                                                                                                                                         | NUMBER:_____                                                                                                                                        |
| C3  | In the past 12 months, have you met a new sexual partner here?                                                                                                                                                                                                                                                                 | 
Yes No
 
1 2
                                                                                                                            |
| C4  | Besides this place, how many other public places have you visited or plan to visit today to socialize, drink alcohol, or look for a person to have sex with?                                                                                                                                                                   | NUMBER:_____                                                                                                                                        |
| C5  | Have you ever had sex?                                                                                                                                                                                                                                                                                                         | 
Yes No
 
1 2
                                                                                                                            |
| C6  | Now I would like to ask about how many men and women you had sex with in the last 4 weeks, including people you had sex with once and people you had sex with more often. In total, how many men did you have sex with in the last 4 weeks?                                                                                    | MEN:_____                                                                                                                                           |
| C7  | In total, how many women did you have sex with in the last 4 weeks?                                                                                                                                                                                                                                                            | WOMEN:_____                                                                                                                                         |

|                                           |                                                                                                                                                                    |                  |         |
|-------------------------------------------|--------------------------------------------------------------------------------------------------------------------------------------------------------------------|------------------|---------|
| C8                                        | Have you had sex with a person in the past 12 months who you never had sex with before? That is, you had sex with him or her the first time in the past 12 months. | Yes
1         | No
2 |
| C9                                        | Have you had sex with more than 10 people in the past 12 months?                                                                                                   | Yes
1         | No
2 |
| C10                                       | Have you had anal sex in the past 12 months with a man?                                                                                                            | Yes
1         | No
2 |
| C10A                                      | Did you use a condom use with your last male partner?                                                                                                              | Yes
1         | No
2 |
| NO.                                | QUESTION                                                                                                                                                    | RESPONSE  |         |
| C11                                       | Have you received money in exchange for sex in the past 12 months?                                                                                                 | Yes
1         | No
2 |
| C11A                                      | Did you use a condom use with your last client?                                                                                                                    | Yes
1         | No
2 |
| C12                                       | Have you ever received money in exchange for sex?
IF NO: GO TO C14.                                                                                             | Yes
1         | No
2 |
| C13                                       | How old were you the first time you received money in exchange for sex?
LEAVE BLANK IF NOT APPLICABLE.                                                          | WRITE AGE: _____ |         |
| C14                                       | In the last 12 months, have you given someone money to have sex?                                                                                                   | Yes
1         | No
2 |
| QUESTIONS ABOUT ACCESS TO SERVICES |                                                                                                                                                                    |                  |         |
| C15                                       | If you wanted a condom, would it be easy to get one?                                                                                                               | Yes
1         | No
2 |
| C16                                       | In the past 12 months, has an outreach worker such as a peer educator given you a condom?                                                                          | Yes              | No      |

|            |                                                                                                                                                               |                                                                                   |
|------------|---------------------------------------------------------------------------------------------------------------------------------------------------------------|-----------------------------------------------------------------------------------|
|            |                                                                                                                                                               | 1 2                                                                               |
| C17        | Do you have a condom with you now?                                                                                                                            | Yes No
1 2                                                                     |
| C18A       | In the last 12 months, have you had any burning when you pee, or discharge from your penis or vagina or anus, or sores on your genitals?                      | Yes No
1 2                                                                     |
| C18B       | IF YES: In the last 12 months, have you sought care for any of these symptoms at a public or private clinic?
IF NOT APPLICABLE (C18=2) THEN CIRCLE 9 (NA). | Yes No NA
1 2 9                                                                |
| C18C       | In the past 12 months Have you been discriminated against by a healthcare worker?                                                                             | Yes No NA
1 2 9                                                                |
| C18D       | At what type of facility did you seek care?                                                                                                                   | dedicated to HIV
general health care
outreach services
referral facility |
| C19        | IF RESPONDENT IS MALE, ASK: Are you circumcised?
IF FEMALE, CIRCLE 9 (NA).                                                                                 | Yes No NA
1 2 9                                                                |
| C20        | How many servings of alcohol have you had in the past 24 hours? A serving is a bottle of beer or a shot of alcohol.                                           | NUMBER:____                                                                       |
| C21        | In the past 12 months, have you received information about HIV or AIDS from an outreach worker at this site?                                                  | Yes No
1 2                                                                     |
| NO. | QUESTION                                                                                                                                               | RESPONSE                                                                   |
| C22        | In the past 12 months, have you received information about HIV or AIDS from the radio?                                                                        | Yes No
1 2                                                                     |

|            |                                                                                                                                                                                                  |                                                 |             |
|------------|--------------------------------------------------------------------------------------------------------------------------------------------------------------------------------------------------|-------------------------------------------------|-------------|
| C23        | In the past 12 months, have you received information about HIV or AIDS from any health worker?                                                                                                   | Yes
1                                        | No
2     |
| C24        | Are you currently seeing a health worker for an HIV infection?                                                                                                                                   | Yes
1                                        | No
2     |
| C25        | Are you currently taking antiretroviral (ART) drugs to treat an HIV infection?                                                                                                                   | Yes
1                                        | No
2     |
| C26        | Now I have a few questions about HIV tests. Have you ever had an HIV test?
IF NO: GO TO C31.                                                                                                  | Yes
1                                        | No
2     |
| C27        | Has a medical provider ever told you that you are infected with HIV, based on an HIV test result? IF NO GO TO C29.                                                                               | Yes
1                                        | No
2     |
| C28        | Think about the first time a medical provider told you that you that you were infected with HIV. Did this occur in the past 3 months? Past 12 months? Or longer ago? IF LONGER AGO, SKIP TO C31. | Past 3 Months
Past 4-12 months
Longer ago | 1
2
3 |
| C29        | Have you been tested for HIV in the past 12 months?
IF NO, GO TO C31.                                                                                                                         | Yes
1                                        | No
2     |
| C30        | IF YES (C29=1) ASK: The last time you were tested, did you get your test result?                                                                                                                 | Yes
1                                        | No
2     |
| C31        | Some people have tried injecting drugs using a needle and syringe. Have you injected any non-prescription drug in the past 12 months?                                                            | Yes
1                                        | No
2     |
| C32        | In the past 12 months, have you shared a needle with another person who was injecting?                                                                                                           | Yes
1                                        | No
2     |
| C33        | Do you currently get health or other services from programs designed for people who inject drugs?                                                                                                | Yes
1                                        | No
2     |
| NO. | QUESTION                                                                                                                                                                                  | RESPONSE                                 |             |

| QUESTIONS TO ASSESS SOCIAL AND ECONOMIC VULNERABILITY                                |                                                                       |                                          |
|--------------------------------------------------------------------------------------|-----------------------------------------------------------------------|------------------------------------------|
| C34                                                                                  | In the past 12 months, have you ever spent a night in jail or prison? | 
Yes    No
 
1      2
 |
| C35                                                                                  | In the past 12 months, have you been hurt physically by the police?   | 
Yes    No
 
1      2
 |
| C36                                                                                  | In the past 12 months, have you used legal services?                  | 
Yes    No
 
1      2
 |
| C37                                                                                  | Have you lived in this area less than a year?                         | 
Yes    No
 
1      2
 |
| C38                                                                                  | Are you currently married or living with a sexual partner?            | 
Yes    No
 
1      2
 |
| C39                                                                                  | Did you complete secondary school?                                    | 
Yes    No
 
1      2
 |
| END OF SURVEY. THANK THE RESPONDENT FOR PARTICIPATING!                               |                                                                       |                                          |
| 
 
Checked by supervisor (signature)_____
 
Date:_____
 
 |                                                                       |                                          |

